# Acronyms and Abbreviations

| ACLS | Advanced cardiopulmonary life support |
| --- | --- |
| APV | Automated pneumatic ventilation |
| ATV | Automatic transport ventilator |
| ABG | Arterial blood gas |
| BVM | Bag-valve-mask |
| CPR | Cardiopulmonary resuscitation |
| COPD | Chronic obstructive pulmonary disease |
| EMT | Emergency medical technician |
| EMT-P | Emergency medical technician - paramedics |
| ETT | Endotracheal tube |
| IO | Intraosseous |
| IV | Intravenous |
| MV | Mechanical ventilation |
| OHCA | Out-of-hospital cardiac arrest |
| RCT | Randomized controlled trial |
| SGA | Supraglottic airway |

# Trial Summary

The prognosis of patients experiencing out-of-hospital cardiac arrest (OHCA) is influenced by multiple factors, with pre-hospital emergency care being particularly critical. In addition to high-quality chest compressions and early defibrillation, effective ventilation is also a key component. With the increasing professionalization of emergency medical personnel, the establishment of advanced airways has become more common. However, ventilation still relies on manual operation, and the ability to provide consistent and effective ventilation without interfering with other resuscitation measures is a significant concern. The use of automatic oxygen delivery devices presents a potential solution.

The PIVOT trial will be conducted in fire department units across Hsinchu County, coordinated by National Taiwan University Hospital Hsinchu Branch. It is scheduled to take place between June 1, 2023, and December 31, 2025. Fire department units will be divided into two groups using bi-weekly cluster randomization: a control group using manual ventilation and an intervention group using automatic oxygen delivery devices. The study will include cases of non-traumatic OHCA reported within the region. The primary objective is to analyze the impact of both groups on patient survival and prognosis, while the secondary objective is to evaluate ventilation parameters and other quality management indicators related to OHCA care.

# Backgrounds

Out-of-hospital cardiac arrest (OHCA) is a critical medical emergency with substantial public health implications. The global incidence of OHCA ranges from 50 to 110 per 100,000 population annually [1]. Despite advances in resuscitation techniques, survival rates remain low, with less than 10% of patients surviving to hospital discharge [2]. The economic burden associated with OHCA is considerable, driven by both direct medical costs and indirect costs such as lost productivity, emphasizing the need for improved resuscitation strategies [3, 4].

In the prehospital setting, emergency medical technicians (EMTs) and paramedics are tasked with numerous responsibilities during resuscitation efforts [5]. These include checking vital signs, establishing intravenous or intraosseous access, administering medications and ensuring adequate chest compression and ventilation while transporting the patients. Effective ventilation is particularly challenging, often performed using a bag-valve-mask (BVM) device. Manual BVM ventilation can be inconsistent and labor-intensive, requiring one or more team members to focus solely on this task, which can detract from other critical resuscitation activities [6].

The American Heart Association (AHA) guidelines currently recommend manual BVM ventilation during cardiopulmonary resuscitation (CPR) [7]. However, this method is fraught with challenges, including the risk of hyperventilation, insufficient ventilation, and interruptions during chest compressions. These issues can compromise the quality of resuscitation and negatively impact patient outcomes.

Mechanical ventilation offers potential advantages over manual BVM ventilation. Studies have demonstrated that mechanical ventilators can provide more consistent and controlled ventilation [8]. For instance, Weiss et al. conducted a study comparing an automatic transport ventilator (ATV) with manual BVM ventilation. The results showed that the ATV allowed EMTs to accomplish additional tasks, improve documentation, and enhance overall patient care [9]. Similarly, the SYMEVECA phase 1 trial indicated that mechanical ventilators provided better ventilatory parameters compared to BVM, although the impact on clinical outcomes needs further investigation [8].

Despite these advantages, most research on mechanical ventilation during CPR has focused on in-hospital settings. The use of automated pneumatic ventilators (APVs) in the prehospital environment remains underexplored. APVs are designed to deliver consistent ventilation with minimal manual intervention, potentially freeing up EMTs to perform other critical tasks during resuscitation. This could be particularly beneficial in prehospital settings where resources and personnel are often limited [9].

There is a significant knowledge gap regarding the effectiveness of APVs as a substitute for BVMs in prehospital OHCA management. Key concerns include whether APVs can deliver sufficient ventilation without causing high plateau pressures that may lead to barotrauma. Addressing this gap is crucial for developing evidence-based guidelines that can enhance prehospital care and improve patient outcomes. This study aims to evaluate the effectiveness of APVs compared to traditional BVMs in the prehospital resuscitation of OHCA patients.

# Literature Review

| No. | Author, year | Title | Study design | Outcomes |
| --- | --- | --- | --- | --- |
| 1 | JA Johannigman, 1995  [10] | Out-of-hospital Ventilation: Bag-Valve Device vs Transport Ventilator | A prospective, nonrandomized sampling comparing ABG between transport ventilator and BVM among intubated out-of-hospital airway management patients. | No differences in ABG data between transport ventilator and BVM groups.  SGA had inadequate ventilation compared to the endotracheal tube. |
| 2 | JJ Osterwalder, 1998  [11] | Effectiveness of mask ventilation in a training mannikin. A comparison between the Oxylator EM100 and the bag-valve device | A RCT comparing ventilatory volume and gastric inflation between APV (peak pressure 50 cm-H_2_O) and BVM on an instrumented manikin. | APV had better tidal volume (1196 vs. 556 mL, p<0.01) with minimal risk of gastric inflation. |
| 3 | SJ Weiss, 2005  [9] | Automatic transport ventilator versus bag valve in the EMS setting: a prospective, randomized trial | A RCT comparing ATV (peak pressure 60 cm-H_2_O) and BVM among OHCA patients using questionnaires completed by EMT. | EMTs were able to accomplish more tasks, document more completely, and provide better patient care with the use of the ATV. |
| 4 | TA Barnes, 2005  [12] | Comparison of an oxygen-powered flow-limited resuscitator to manual ventilation with an adult 1,000-mL self-inflating bag | The model study compared the volume delivered to lungs and stomach between the Oxylator and BVM. | The volumes delivered with the Oxylator and the BVM to the lungs and stomach were not significantly different. |
| 5 | Salas N, 2007  [13] | Comparison of ventilation and cardiac compressions using the Impact Model 730 automatic transport ventilator compared to a conventional bag valve with a facemask in a model of adult cardiopulmonary arrest | The randomized crossover quasi-experimental study compared the volume delivered to lungs and stomach between ATV and BVM on the instrumented manikin | There were no differences in tidal volume between 2 groups, but BVM let more air into the stomach (137 vs. 14mL, p<0.05). |
| 6 | X Hu, 2013  [14] | The effects of an automatic, low pressure and constant flow ventilation device versus manual ventilation during cardiovascular resuscitation in a porcine model of cardiac arrest | The pig model study compared the ventilation parameters between APV and BVM. | Ventilation with APV during CPR provides adequate ventilation compared to BVM. |
| 7 | C Kill, 2014  [15] | Mechanical Ventilation During Cardiopulmonary Resuscitation With Intermittent Positive-Pressure Ventilation, Bilevel Ventilation, or Chest Compression Synchronized Ventilation in a Pig Model | The animal study compared the ABG, blood pressure and ROSC between 3 types of ventilation:  intermittent positive-pressure ventilation (IPPV), bilevel ventilation, and chest compression synchronized ventilation | IPPV and bilevel ventilation showed similar ventilation and oxygenation.  Chest compression synchronized ventilation elicited the highest mean arterial pressure and best oxygenation |
| 8 | LBA Neumamm, 2021  [16] | Empirical evidence for safety of mechanical ventilation during simulated cardiopulmonary resuscitation on a physical model. | The manikin study compared the ventilation and peak pressure during chest compression among 3 types of ventilation:  volume-controlled (VCV), pressure-controlled (PCV), pressure regulated volume-controlled (PRVC). | Ventilator use during chest compression resulted in pressure and volume similar to BVM. |
| 9 | S Orlab, 2021  [17] | Reliability of mechanical ventilation during continuous chest compressions: a crossover study of transport ventilators in a human cadaver model of CPR | By using human cadaver, the study  compared tidal volumes between 3 transport ventilators. | All transport ventilators can provide good ventilation even though chest compression considerably decreases tidal volumes. |
| 10 | A Hernández-Tejedor, 2023  [8] | Ventilatory improvement with mechanical ventilator versus bag in non-traumatic out-of-hospital cardiac arrest: SYMEVECA study, phase 1 | A pragmatic prospective nonrandomized trial comparing ABG, patient outcome on OHCA patients between  MV( peak pressure 50 cm-H_2_O) and BVM. | MV had better ventilation than BVM,  but no difference between outcomes. |
| 11 | T Tangpaisarn, 2023  [18] | The effects of mechanical versus bag-valve ventilation on gas exchange during cardiopulmonary resuscitation in emergency department patients: A randomized controlled trial (CPR-VENT) | In cardiac arrest patients in ED, the RCT compared ABG parameter, patient outcome and pneumothorax between  MV( peak pressure 60 cm-H_2_O) and BVM. | The ABG parameter, patient outcome and pneumothorax showed no differences between 2 groups. |
| 12 | J Shin, 2024  [19] | Automatic Mechanical Ventilation vs Manual Bag Ventilation During CPR: A Pilot Randomized Controlled Trial | A pilot RCT comparing ABG parameter, ventilation and patient outcome in OHCA patients between  MV( peak pressure 70 cm-H_2_O) and BVM. | MV had lower tidal volume (267 vs. 507mL, p<0.001) and lower minute ventilation (3.1 vs. 6.7L p=0.009),  but no difference between outcomes.  No ABG parameters difference between groups. |

# Trial Design

This trial is a pragmatic, open-label, multi-center cluster randomized controlled trial.

## Hypothesis

The hypothesis of the trial was formulated using the PICO framework (Population-Intervention-Comparison-Outcome). The study focused on non-traumatic out-of-hospital cardiac arrest (OHCA) patients in Hsinchu County (Population). It hypothesized that patients treated with advanced airway management and automated pneumatic ventilation (Intervention) would achieve a higher rate of return of spontaneous circulation (ROSC) (Outcome) compared to those who received bag-valve-mask ventilation (Comparison).

## Objective

The primary objective of this trial is to evaluate the clinical effectiveness of the automated pneumatic ventilation (APV) method in prehospital resuscitation of out-of-hospital cardiac arrest (OHCA) compared to the bag-valve-mask (BVM) method. The primary outcome is any return of spontaneous circulation (ROSC).

The secondary objectives include:

1. Comparing the ventilation parameters between the APV and BVM methods.
2. Evaluating the overall resuscitation quality in the APV and BVM groups.
3. Comparing the satisfaction levels of emergency medical technicians between the APV and BVM groups.

## Inclusion criteria

Adult out-of-hospital cardiac arrest with attempted resuscitation by the Hsin-chu County Emergency Medical Service.

## Exclusion criteria

- - 1. Pregnancy
    2. Died from trauma
    3. ROSC before EMS arrival
    4. Dead on arrival (reaching conditions such as decomposition, rigor mortis severe burns, decapitation, evisceration, or trunk fracture)
    5. Refusal of medical treatment by family members
    6. No placement of an advanced airway throughout the procedure

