## Randomization and blinding

The participating EMS teams will be divided into two randomized clusters. Each cluster will be assigned to either the APV or BVM group. The duration of a cluster is 14 days (two weeks). The study center will instruct the clusters to alternate between APV and BVM according to a sequence determined by random allocation.

The randomization process was done by a research assistant. The sequence was generated using tool by Sealed Envelope Ltd. 2022 [20]. The formula this program used is based on the textbook *Clinical Trials: A Practical Approach* [21]. In the program, the seed is generated by a random table by Microsoft Excel. Each block contains 6 clusters. However, the EMTs are not aware of the randomization and allocation method.

The allocation sequence will be revealed until three days before the next cluster begins via social network application.

Blinding of the EMTs or hospital staff is not feasible because the ventilation equipment used in the study cannot be blinded

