## Study procedures and workflow

- - 1. Weekly Group Assignment Announcement

Every Friday evening, the group allocation results are announced via the study group's communication app. If assigned to the intervention group, the paramedics must ensure that the APV device is functioning properly and place it in the ambulance. If allocated to the control group, the device should be removed from the ambulance. The new round of group allocation will begin on Monday at 8 AM.

- - 1. OHCA rescue

When the dispatch center reports an OHCA case, an OHCA is identified on scene, or a patient experiences cardiac arrest during transportation to the hospital, the EMTs will confirm whether the case meets the inclusion criteria. The EMTs will then perform ACLS and determine which advanced airway (ETT or SGA) to use based on the situation at the scene.

The standard ACLS procedure in Hsin-chu county is provided in Appendix 1.

- - 1. Device Setup After Establishing Advanced Airway

After establishing the advanced airway (SGA or ETT), the following equipment should be connected under the following sequence:

Patient → Endotracheal tube or supraglottic airway → HEPA filter → AccuVent sensor → End-tidal CO2 sensor → Automatic ventilator → Oxygen tank (Figure 1).

- - 1. Data Entry After Rescue

After completing the rescue, upon returning to the fire department, the EMT should log the case data into an Excel form and upload the rescue reporting form. Additionally, they should complete the satisfaction questionnaire after every successful patient recruit.

These data are stored in a secure database.

- - 1. Data Export from Zoll X-series

A designated staff member will export the case’s ventilation and chest compression physiological data from the Zoll X-series monitor and then upload to a secured database.

Figure 2. Equipment connection for enrolled OHCA patients.

[figure not shown]

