# Analytic Plan

Statistical Package for the Social Sciences (version 26.0; IBM Corp., Armonk, NY, USA) will be used for the statistical analyses in this study. Intention to treat analysis will be adopted for comparing outcomes between interventions. Firstly, descriptive statistics of demographics (Table 1), ventilation parameters (Table 2), and outcomes (Table 3) among APV group and BVM group will be presented as number (percentage) for categorical variables and median (interquartile range) for continuous variables. Categorical variables will be compared using Pearson’s chi-square test or Fisher’s exact test, while continuous variables will be compared using Mann–Whitney U test. Secondly, multivariable logistic regression will be conducted to investigate the association of different ventilation interventions and patients’ outcomes, adjusting for potential confounders. Subgroup analysis, presented as a forest plot, will also be performed to investigate the impact of different interventions on outcomes in different subgroups. We will also compare the adjusted absolute difference between ventilation parameters measured in the APV and BVM group using the linear mixed-effects model (LMM). For the LMM, variables including demographics, prehospital information, resuscitation managements were included as fixed effects, whereas each patient will be modeled as a random effect. Two tail p-values <0.05 will be considered as statistically significant and will be corrected with Bonferroni correction in post-hoc analyses.

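### The family-refusal exclusion has no time point, so it permits patients to be excluded after treatment has begun with the arm known, which does not fit the stated intention-to-treat analysis

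*Protocol*

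**What the plan says.** The protocol's inclusion criterion is "Adult out-of-hospital cardiac arrest with attempted resuscitation by the Hsin-chu County Emergency Medical Service". Among the exclusions, item 5 is "Refusal of medical treatment by family members", with no time point, no statement of which treatment is refused and no statement of who decides. Two neighbouring items differ in kind. Item 4, "Dead on arrival (reaching conditions such as decomposition, rigor mortis severe burns, decapitation, evisceration, or trunk fracture", is a fact fixed before the crew acts. Item 6, "No placement of an advanced airway throughout the procedure", can be judged only once the attempt is over.

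Allocation is by 14-day period and reaches crews in advance: "Every Friday evening, the group allocation results are announced via the study group's communication app". On masking, Randomization and blinding says: "Blinding of the EMTs or hospital staff is not feasible because the ventilation equipment used in the study cannot be blinded". In the workflow, "the EMTs will confirm whether the case meets the inclusion criteria. The EMTs will then perform ACLS"; the exclusion criteria are not mentioned at that step. The case is logged after the rescue, when the crew is back at the station.

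Under Outcome measurement, any ROSC counts whether it occurs before hospital or after in-hospital resuscitation. The Ethics section waives consent for all participants, so item 5 concerns refusal of treatment, not withdrawal from research. The Analytic Plan says "Intention to treat analysis will be adopted for comparing outcomes between interventions", without further definition of the set.

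**The concern.** If the family refuses before any attempt, the patient fails the inclusion criterion and item 5 adds nothing. The item changes the analysed population only where an attempt was made and a refusal also occurred. Nothing in the wording stops it from being applied on scene, in transit or in hospital, while the outcome is still open.

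An exclusion of that kind depends on an event during care, is made by people who know the arm, and can be tied to the outcome: stopping at the family's request means no ROSC unless ROSC has already occurred. If refusals differ by arm, the comparison of ROSC is biased. If they do not, both ROSC rates may still describe a selected group.

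**Working it through.** **1. Where item 5 has an effect.**

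| Situation | Eligible without item 5? | Does item 5 change the set? |
|---|---|---|
| Refusal before any EMS attempt | No, inclusion fails | No |
| Refusal after the attempt starts, no advanced airway ever placed | No, item 6 applies | No |
| Refusal after the airway is placed, before ROSC | Yes | Yes, removes a patient who may have no ROSC |
| Refusal of further care after ROSC | Yes | Yes, removes a patient with ROSC |

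The third and fourth rows are where the item matters. Both lie after treatment has begun with the arm known.

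**2. The plan's own figures.** They have no bearing on the logic but supply the arm size used below. With proportions 0.567 and 0.433, two-sided alpha 0.05 and power 0.80, the two-proportion formula gives 218 per arm, 436 in total. Then 436 × 1.12 = 488.3, taken as 488, and 488 / 0.95 = 513.7, rounded up to 514, or 257 per arm. The stated figures reproduce.

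**3. Illustration.** The document gives no refusal rate, so every removal rate here is an assumption. If a fraction f of an arm is removed and none of those removed had ROSC, the observed rate is p / (1 − f).

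No true effect, 5% removed from one arm and 10% from the other:
- p = 0.433: 0.433 / 0.95 = 45.6% and 0.433 / 0.90 = 48.1%, a false difference of 2.5 points.
- p = 0.50: 0.50 / 0.95 = 52.6% and 0.50 / 0.90 = 55.6%, a false difference of 2.9 points.

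The chance of p < 0.05 in these scenarios uses a pooled z test with effective size 257 / 1.12 = 229.5 per arm before removal:

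| Removed (arm A / arm B) | False difference, p = 0.433 | Chance of p < 0.05 | False difference, p = 0.50 | Chance of p < 0.05 |
|---|---|---|---|---|
| 5% / 5% | 0 | 5.0% | 0 | 5.0% |
| 10% / 10% | 0 | 5.0% | 0 | 5.0% |
| 5% / 0% | 2.3 points | 7.7% | 2.6 points | 8.6% |
| 10% / 5% | 2.5 points | 8.2% | 2.9 points | 9.3% |
| 10% / 0% | 4.8 points | 17.2% | 5.6 points | 21.3% |

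Under the planned effect, equal removal of 5% moves the difference from 13.4 points to 0.567 / 0.95 − 0.433 / 0.95 = 59.7% − 45.6% = 14.1 points.

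**4. Direction.** If those removed all had ROSC, the observed rate is (p − f) / (1 − f). At p = 0.433, 5% against 10% gives 0.383 / 0.95 = 40.3% and 0.333 / 0.90 = 37.0%, a false difference of 3.3 points the other way. The sign therefore depends on who is removed, and the document does not say.

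**The case against.** Redundancy with the inclusion criterion does not prove late use. The dead-on-arrival item is largely redundant in the same way, so the list may simply restate ordinary reasons for not enrolling. Item 6 says so when it means the whole course of the attempt; item 5 does not. The workflow puts the eligibility check before ACLS, so refusal when the crew arrives is a natural reading. This stands against any claim that item 5 can act only after resuscitation has started. It does not close the gap, because refusal, unlike death on arrival, can happen at any time, and the workflow step names only the inclusion criteria.

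A reader might also infer that the rule removes mostly treatment failures. That is plausible if families stop an ongoing attempt, but no text or figure supports it, and refusal after ROSC would remove successes.

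Nor does the protocol flatly contradict intention to treat. With allocation by period, every patient-level exclusion follows allocation, and one resting on a fact fixed before treatment and unaffected by it is compatible with the principle. The conflict arises only if refusals after the start of treatment are excluded, which the text permits but does not state.

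Three further points stand. Stops before airway placement already fall under item 6, so the separate effect of item 5 is confined to a subset of unknown size. No reason is given why families would refuse differently by device. The flow diagram and any SAP are not at hand and may treat refusals more fully.

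**Conclusion.** The concern holds in limited form. Item 5 is undated, has its effect mainly after EMS has begun, and so permits unblinded exclusion of treated patients for an event that can be related to the outcome. Such exclusions do not fit the unqualified intention-to-treat statement. It is not shown that they occur, that they fall mainly on patients without ROSC, or that they differ by arm.

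The size is therefore unknown. When those removed all lack ROSC, a false difference under the null needs unequal removal. The 2.5 to 2.9 points for 5% against 10%, set against a planned 13.4, rest on that assumption and on assumed rates. Equal removal then leaves the null difference at zero and only raises both rates. The point still merits a change, because the protection is specific and almost free.

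**What to change.** In the exclusion criteria, limit item 5 to refusal recorded before EMS starts resuscitation. The item then mostly repeats the inclusion criterion, which is harmless and removes the ambiguity.

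In the Analytic Plan, state that a patient who meets all other criteria, including advanced airway placement, and whose family refuses later stays in the intention-to-treat set under the arm allocated for that period. The outcome is the one observed: no ROSC unless ROSC had already occurred. Report later refusals by arm and timing in the flow diagram. If any records have already been excluded for later refusal, restore them before analysis.

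The cost is a line in each of two sections, possibly slightly lower ROSC rates, and retrieval of any restored records. The change governs only who is analysed and has no bearing on how families' wishes are handled or on clinical care.

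### The exclusion for no advanced airway is applied after open allocation, so the set labelled intention to treat is open to selection bias if airway placement, or its timing relative to ROSC, differs by arm

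*Protocol*

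**What the plan says.** All references are to the Protocol.

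- **Population.** Inclusion criteria: "Adult out-of-hospital cardiac arrest with attempted resuscitation by the Hsin-chu County Emergency Medical Service". Exclusion criteria, item 6, then removes patients with "No placement of an advanced airway throughout the procedure". Item 3 excludes ROSC only when it occurs before EMS arrival.
- **Knowledge of the arm.** Randomization and blinding: "The allocation sequence will be revealed until three days before the next cluster begins via social network application", and "Blinding of the EMTs or hospital staff is not feasible because the ventilation equipment used in the study cannot be blinded". Study procedures and workflow: "If assigned to the intervention group, the paramedics must ensure that the APV device is functioning properly and place it in the ambulance". In control periods the APV is taken out of the vehicle.
- **Who judges eligibility.** Study procedures and workflow: when an arrest is reported or identified, "the EMTs will confirm whether the case meets the inclusion criteria". The same crews then manage the airway.
- **Outcome.** Outcome measurement: the primary outcome is any ROSC, prehospital or after in-hospital resuscitation.
- **Analysis.** Analytic Plan: "Intention to treat analysis will be adopted for comparing outcomes between interventions". It does not say whether patients removed under item 6 are counted.

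**The concern.** Intention to treat protects a comparison because membership of each group is settled before allocation can affect it. Here membership is settled later. An arrest attended in an APV period enters the analysis only if an advanced airway is placed, and the people placing it know which period they are in. The APV connects only through that airway, so in an APV period placement is also the gateway to using the device.

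Exclusion can depend on the outcome as well. A patient who regains circulation after EMS arrival but before airway placement, and never receives an airway, is dropped although the primary outcome has occurred. If an airway is placed anyway, the same patient counts as a success.

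If placement or its timing differed by arm, the analysed groups could differ in prognosis with no treatment effect. Adjusting for measured covariates could not be relied on to correct this. If the excluded arrests are not recorded by arm, the problem could not be assessed afterwards either.

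**Working it through.** **Sequence.** Allocation of the 14-day period → crews told about three days ahead → APV loaded or removed → arrest attended → eligibility checked by the crew → airway placed or not → item 6 applied. The exclusion falls after every point at which the arm is known.

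**The plan's own figure.** Sample Size Estimation uses ROSC of 0.567 and 0.433, two-sided alpha 0.05, power 0.80 and 1:1 allocation. The pooled-variance two-proportion formula gives 218 per arm, 436 in total. Then 436 × 1.12 = 488.3, taken as 488, and 488 / 0.95 = 513.7, so 514. The figure reproduces. The planned effect is 56.7 − 43.3 = 13.4 points.

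**Illustrative bias.** The Protocol gives no placement rates, so these are assumptions. Let a_B and a_A be the placement proportions under BVM and APV. Let ROSC be 43.3% in patients who would receive an airway in either arm, and q in the extra patients who receive one only under APV. There is no true effect.

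Bias = [a_B × 0.433 + (a_A − a_B) × q] / a_A − 0.433 = [(a_A − a_B) / a_A] × (q − 0.433)

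With a_B = 0.80:

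| a_A | q = 0.20 | q = 0.70 | q = 1.00 |
|---|---|---|---|
| 0.85 | −1.4 points | +1.6 points | +3.3 points |
| 0.90 | −2.6 points | +3.0 points | +6.3 points |

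For example, a_A = 0.90 and q = 1.00 gives (0.10 / 0.90) × 0.567 = 0.063. The bias is zero if a_A = a_B or if q = 0.433. If placement were instead higher under BVM, the signs reverse.

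**Effect on the error rate.** The effective size per arm is 488 / 1.12 / 2 ≈ 218, so the standard error is √(2 × 0.433 × 0.567 / 218) = 0.0475. The nominal 5% two-sided error becomes about 6% at −1.4 or +1.6 points, 8–10% at −2.6 to +3.0 points, and 26% at +6.3 points.

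**Power if all eligible arrests were the primary set.** Assume the planned effect in airway patients, no effect in the others, and all arrests taken from the same clusters. With placement proportion a, the difference is 0.134 × a and N = 488 / a. If clusters grow to 3 / a patients, the design effect is 1 + (3/a − 1) × 0.06.

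| a | Difference | N | Power, design effect 1.12 | Power, larger clusters |
|---|---|---|---|---|
| 0.90 | 12.1 points | 542 | 76% | 75% (design effect 1.14) |
| 0.80 | 10.7 points | 610 | 71% | 69% (design effect 1.165) |

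**The case against.** The strongest reply is that the restriction follows the question. The Hypothesis section asks about advanced airway management with APV, Exposure management connects both devices through an advanced airway, and care is meant to differ only after placement. If placement were unaffected by arm, restricting to airway patients would be harmless. This stands as a reason to keep the cohort. It does not make the cohort an intention-to-treat set, because nothing in the text makes placement independent of arm.

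Second, a reader might infer that crews are free to decide whether to place an airway, and that APV periods change that decision. The text does not say so. Exposure management and Study procedures and workflow describe the choice between SGA and ETT, and falling back to an SGA after two failed ETT attempts suggests that placement is expected. The local ACLS procedure (Appendix 1) is not shown and may standardise it. The objection stands: differential placement is a possibility, not a finding.

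Third, individuals are not randomised, and the intention-to-treat sentence could mean analysing enrolled patients by allocated arm, including those switched to BVM after an APV malfunction. That reading is fair, and a statistical analysis plan or the CONSORT figure, neither of them shown, may define or count the set. But the exclusion itself is fixed in the Protocol's eligibility criteria, so the label needs qualifying there.

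Fourth, losing patients with ROSC before placement is not a separate source of bias. With no arm difference in placement or its timing, it affects both arms alike. This also stands.

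**Conclusion.** The point holds as a vulnerability in how the analysis set is defined. Item 6 acts after open allocation, on a step performed by crews who know the arm, so the set called intention to treat is not all eligible arrests attended under that arm. Bias follows only if placement, or its timing relative to ROSC, differs by arm.

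The size is illustrative and the direction unknown. Under the assumed rates it is about −2.6 to +3.0 points, against a planned effect of 13.4. The +6.3 figure needs both a 10-point difference in placement and ROSC already present in every extra APV patient.

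Two stronger readings are not supported. One is that the primary comparison is biased: the Protocol contains no placement rates and shows no arm difference. The other is that item 6 has to be dropped from the primary set: that would move the target population away from the stated hypothesis and lower power to about 76% at 90% placement and 69–71% at 80%.

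**What to change.** 1. Keep the advanced-airway cohort as the primary set, but call it modified intention to treat in the Analytic Plan and state that item 6 is applied after allocation.
2. Log every attended adult non-traumatic arrest with attempted resuscitation that meets the other criteria, by allocated arm, including those removed under item 6.
3. Report airway placement, time to placement, and ROSC before placement, by arm.
4. Pre-specify any ROSC in all eligible arrests, by allocated arm, as the key sensitivity analysis.

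**Cost.** The primary analysis loses no power. Data Collection and Follow-up already takes SGA, ETT and prehospital ROSC from the rescue reporting form. It does not list the time of placement or whether ROSC came before it, so those items may need adding. Hospital ROSC must be obtained for the excluded arrests, and the Ethics section requires IRB approval for any modification.

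Making the all-arrest set primary remains open to the sponsor, at the loss of power and change of question given above. It is not a required change.
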